##### External facilitation

External facilitation in the SSL follows the protocols outlined in the Implementation Sustainment Facilitation strategy, which has demonstrated effectiveness in a cluster randomized trial [40]. The SSL facilitator will use the publicly available facilitator workbook, meeting agendas, and worksheets for the Implementation Sustainment Facilitation strategy [41].

Throughout the Preparation phase, the SSL facilitator will hold monthly site-specific meetings to prepare for CM implementation. Topics covered in these meetings will include: discussing the goals of the implementation initiative; encouraging staff to attend training; addressing any emergent issues related to staff engagement in training; and increasing organizational preparedness for CM implementation. In addition, the facilitator will conduct an in-person site visit to engage in strategic planning for CM workflow integration. Data from the scales given at the start of the preparation phase (leadership engagement, implementation climate, CM attitudes) will be used to identify potential barriers and facilitators to CM implementation and to develop a plan to address them. The meeting will also consist of a CM process walkthrough. A major focus will be on ensuring that the necessary resources will be allocated to launch CM.

#### Implementation phase

When preparation activities are complete, OTPs shift into the active Implementation phase lasting 4 months. The goal of this phase is to commence CM implementation and integrate it into the usual workflow.

##### Didactic training

The team’s CM expert will offer monthly calls for OTPs. These calls give OTP counselors and leaders the chance to ask questions about CM techniques. Call content will focus on building CM knowledge and awareness and will not be focused on implementation.

##### Performance feedback

CM fidelity monitoring will be enhanced by the CM Tracking Tool, an Excel tracking tool developed by the study team. The tool prompts counselors to complete a brief Weekly Report for each CM patient. Each report takes 2–3 min to complete and collects date of the CM session; results of the stimulant urine screen; number of CM draws administered; and specific draws received. It also contains the first 6 items of the CM Competence Scale, which counselors complete as a self-reported fidelity check. Data input into the CM Tracking Tool yield a user-friendly dashboard for counselors that shows each patient’s progress through the CM program, summarizes fidelity of CM delivery, and automatically calculates the number of draws earned and number of draws anticipated in the next session. The CM Tracking Tool is used as the basis of a recommended EMR build for the OTPs and serves as a viable low-tech alternative.

##### External facilitation

In addition to monthly calls with a CM expert, OTP counselors and leaders will have monthly site-specific meetings with an external facilitator, following the protocols from the Implementation Sustainment Facilitation workbook [41]. Facilitation meetings are used to review each OTP’s implementation progress and discuss ways to improve performance. In the final month, the facilitator will lead a sustainment-centered planning retreat to (a) review center performance during the Implementation phase, (b) discuss the extent to which, and how, the center plans to continue CM implementation; and (c) develop a concrete sustainment action plan. Given that inadequate funding is a key barrier to CM sustainment, a primary focus of the facilitator’s work will be helping organizational leadership to evaluate a range of options to financially support CM, including soliciting prize donations, applying for grant funding, and/or applying for state funding.

#### Sustainment phase (remaining wedges)

The focus of this phase is having OTPs sustain CM without formal support. OTPs will continue to have access to the CM tracking tool and to the monthly all OTP calls with a CM expert. OTPs will also be encouraged to provide ongoing performance feedback to CM counselors as part of their ongoing operations.

#### Provider turnover plan

Throughout each stage of the SSL, we anticipate that a substantial proportion of counselors and leaders who consent will leave their OTP or the field entirely, and that new providers will come on board. Provider turnover research [42–44] estimates an annual turnover rate of approximately 30% among substance use disorder front-line counselors and 20% among OTP leadership. Our more recent experiences with OTPs recorded comparable rates: 32% of counselors turned over within our 6-month active implementation phase.

To address turnover, a key focus of the SSL strategy is on building the capacity of OTP leadership to provide ongoing support. We video- or audio-record SSL training and facilitation activities so leaders have easily transferrable, low-cost training materials, consistent with usual practices at the New England ATTC. Recommended training of replacement providers will consist of watching and/or listening to recordings of SSL activities. Most critically, CM providers will be required to conduct a role play that meets the CM Competence Scale benchmark before being approved to implement CM. Any time a role play is submitted by a replacement provider, a site leader will be encouraged to review it and submit their own CM Competence Scale rating. This will provide ongoing opportunities for leaders to gain practice rating CM sessions for fidelity and to compare ratings to those given by research staff.

### Sources of data

Data are collected via multiple methods, including EMR data extraction, provider surveys, and research team observational measures, described in detail below.

#### EMR extraction and CM tracking tool

OTPs will document CM session delivery in their usual session records within their existing EMR systems and extract a de-identified dataset including all patient encounters at six time points (start and end of each wedge). OTPs will also be given the Excel CM Tracking Tool to facilitate ongoing tracking and provision of real-time feedback, and those OTPs that opt to use the tool will be asked to send the Excel tracker at the same six time points. De-identified data from all available patient records will be identified by each site to allow the study team to calculate key study variables at each OTP including reach, effectiveness (patient abstinence and treatment retention), adoption, implementation, and maintenance.

#### Provider surveys and team-based inventory

CM providers (i.e., both counselors and leaders) will complete three online surveys to assess contextual determinants at the provider level. The provider surveys will be administered at three timepoints: at the start of each OTP’s Preparation phase, midpoint of their Implementation phase, and endpoint of their Implementation phase. In addition, CM providers at each OTP will be asked to collaboratively complete a team-based inventory of contextual determinants of implementation at the start of the Preparation phase.

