**Fig. 1 Fig1:**
[figure not shown]
Stepped wedge design and timeline. Ten opioid treatment programs are randomized to crossover from usual care (depicted in grey) to receipt of the Science to Service Laboratory across four wedges. The Science to Service Laboratory consists of preparation activities (depicted in blue) and active implementation activities (depicted in yellow). Following 6 months of active Science to Service Laboratory support, the programs shift into a sustainment phase (depicted in green) during which they receive minimal support. Programs provide data at the 0, 6, 12-, 18-, 24-, and 30-month marks

During the first wedge, two OTPs will be randomly selected to crossover from usual care into the SSL implementation strategy condition. These two OTPs receive the SSL elements corresponding to the Preparation and Implementation phases of implementation. During the second wedge, the next cohort of two OTPs receives the SSL elements corresponding with the Preparation and Implementation phases and the first cohort shifts to the Sustainment phase, during which SSL activities are stopped and sustainment is tracked. The crossover pattern continues until all OTPs have received active SSL support. Randomization will be done using a random number generator prior to the start of each wedge by the study statistician. Immediately after randomization, he will inform the study team, who will commence scheduling of Preparation activities with the randomly selected sites. To ensure decoupling of financial support with the randomization to the SSL, OTPs receive a flat stipend each year that they participate in the study.

A key benefit of the stepped wedge trial is the extended timeline to measure sustainment. Over a 30-month study, the stepped wedge design allows the first wedge to provide sustainment data for up to 24 months.

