#### Preparation phase

Each wedge begins with 2 months of Preparation activities. At the start of this phase, counselors and leaders will complete the first of three provider surveys and a team-based inventory.

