### Study measures

To address Specific Aim 1 (implementation effectiveness), we measure the following implementation outcomes: Reach, Adoption, Implementation, Maintenance, and Equity [45]. To evaluate Specific Aim 2 (patient effectiveness), we measure two patient outcomes in line with the Effectiveness element of RE-AIM: Stimulant Abstinence and Treatment Retention. Finally, in pursuit of Specific Aim 3 (exploratory mediators), we evaluate contextual determinants as putative mediators of implementation outcomes; specifically, we assess implementation strategy progress, inner setting factors, and provider characteristics. Table 1 presents a detailed overview of study measures by Specific Aim.

**Table 1 Tab1:** Description of study measures, data source, and timing of measurement

Outcome	Definition	Data source	Frequency and timing of measurement
*Aim 1*			
Reach	Calculates patients’ exposure to contingency management (CM) by dividing the number of newly admitted patients with recent stimulant use (defined as documented patient-reported stimulant use or a positive stimulant urine screen within the first 30 days of treatment) who received 1 or more CM encounters by the total number of newly admitted patients with recent stimulant use.	Electronic medical records (EMR) CM tracking tool	End of each wedge
Adoption	Calculates the proportion of providers who have adopted CM by dividing the number of counselors who delivered 1 or more CM encounters divided by the total number of counselors.	EMR CM tracking tool	End of each wedge
Implementation	Assesses delivery of CM with fidelity in two ways: 1. Proportion of counselors meeting the fidelity target on the CM Competence Scale (a mean overall score ≥ 4.0), which rates 9 CM elements on a scale from 1 (not at all present) to 7 (fully present) 2. Proportion of CM sessions covering ≥ 7 of 9 of the standard CM elements, as assessed by a self-report checklist in the CM tracking tool.	Observer rating CM tracking tool	Role play following Preparation phase End of each wedge
Maintenance	Measures Reach, Adoption, and Implementation throughout the Sustainment phase.	EMR CM tracking tool Observer rating	End of each wedge during Sustainment phase
Equity	Evaluates whether the above systematically vary based on race/ethnicity, biological sex, gender, and other sociodemographic factors of patients and providers.	EMR Provider survey	Baseline
*Aim 2*			

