Aim 1 hypotheses (effect of SSL on CM Reach and CM Adoption) will be tested by examining the effect of treatment condition at a given center at a given time point, for patients nested in counselors in centers (3-level model). Generalized linear mixed models will be used to evaluate treatment effects on rates of CM Reach, Adoption, and Maintenance.

For Aim 2 analyses, generalized MSEM models will be used to model the effect of SSL implementation. Using data from prior CM trials, we assume a rate increase for Stimulant Abstinence from 25 to 40% following SSL receipt, and a treatment retention increase of 30% from 9 to 12 weeks following SSL.

For Exploratory Aim 3 analyses, MSEM models will be used to assess whether putative provider-level mediators that will be assessed via the provider surveys (e.g., implementation climate, implementation leadership, CM perceptions) are associated with change in implementation outcomes. Exploratory outcome analyses will measure putative mediators as latent factors combining measures of SSL fidelity, inner setting factors, and provider characteristics, to assess the extent to which latent factors serve as mechanisms of action for the main effect of the SSL on implementation outcomes using bootstrapped confidence intervals.

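### Aim 3: both post-baseline provider surveys come after CM delivery has begun, so for same-wedge Reach and Adoption the planned analysis cannot tell a mediator from a consequence

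*Protocol article*

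**What the plan says.** The section on provider surveys and the team-based inventory schedules three surveys for each OTP: one when its Preparation begins, then two more at the "midpoint of their Implementation phase, and endpoint of their Implementation phase". Table 1 repeats these timepoints for the climate, leadership, acceptability/appropriateness/feasibility and CM attitude scales.

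The phase lengths are fixed in the SSL description. "Each wedge begins with 2 months of Preparation activities", after which "OTPs shift into the active Implementation phase lasting 4 months". On the second phase the protocol says "The goal of this phase is to commence CM implementation and integrate it into the usual workflow". The Fig. 1 legend closes the sequence: "Following 6 months of active Science to Service Laboratory support, the programs shift into a sustainment phase".

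Table 1 defines Adoption by "dividing the number of counselors who delivered 1 or more CM encounters divided by the total number of counselors". Reach likewise needs a single CM encounter per patient. Both are read at the end of each wedge.

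The Data analysis section says that Aim 3 will look at whether the surveyed factors are associated with change in implementation outcomes. It then assesses how far "latent factors serve as mechanisms of action for the main effect of the SSL on implementation outcomes", using bootstrapped confidence intervals. It links no survey wave to a later outcome period.

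**The concern.** A mediator has to come before the outcome it is said to explain. Here a counselor counts as an adopter from one CM encounter, which may occur before the midpoint survey and, for anyone who adopts in the active wedge, will have occurred by the endpoint survey. The scales ask how acceptable, feasible and effective CM is and how far the organization supports it. Someone who has just delivered CM has first-hand grounds to answer differently, so delivery can move the score.

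At stake is what Aim 3 is for: showing how the SSL works. The Discussion presents the study of contextual determinants as a contribution on why and how implementation strategies work. A finding that attitudes and climate explain the SSL effect could arise even if they had no influence on delivery. Bootstrapped intervals deal with sampling error, not with direction.

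**Working it through.** **1. The calendar.** Inputs: 10 OTPs, 8 patients per OTP per month and 30 months (Organization-level recruitment; Fig. 1); four wedges, taken as starting at months 0, 6, 12 and 18, with an average of 2.5 OTPs each; six months of active support. The protocol's expected EMR pulls by phase are then reproduced:

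- Usual care: 2.5 × (0 + 6 + 12 + 18) × 8 = 720
- Preparation/Implementation: 10 × 6 × 8 = 480
- Sustainment: 2.5 × (24 + 18 + 12 + 6) × 8 = 1200

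These match the Data analysis section, so Preparation plus Implementation fills exactly one six-month wedge.

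**2. Surveys against delivery, in wedge months.**

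| Event | Month |
|---|---|
| Survey 1 (start of Preparation, before SSL exposure) | 0 |
| CM delivery begins | about 2 |
| Survey 2 (mid-Implementation) | 2 + 4/2 = 4 |
| Survey 3 (end of Implementation) | 2 + 4 = 6 |
| Reach and Adoption read for the active wedge | 6 |

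Survey 1 can serve only as a baseline. Survey 2 comes halfway through the delivery period, and survey 3 after all of it. Only the 1200 Sustainment pulls come after survey 3.

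**3. Which contrast carries the main effect.** Table 2 gives the comparison for Reach and Adoption as usual care against preparation/implementation. That is the wedge in which survey and outcome overlap. Its Maintenance row compares preparation/implementation with sustainment.

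**4. How much it could matter (illustration).** From Table 2: 70 counselors per condition, Adoption 10% v 50%. Assumed: the mediator has no effect on Adoption; the later score is M = g × Adoption + N(0,1); both conditions supply a score. The indirect effect is a × b, with a from regressing M on condition and b from regressing Adoption on condition and M. False mediation means that a and b are both significant at two-sided .05, or that a 95% interval for a × b lies above zero. The true indirect effect is zero throughout.

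| g (SD) | Runs declaring false mediation |
|---|---|
| 0 | about 0.1% |
| 0.2 | about 1% |
| 0.3 | about 3% |
| 0.5 | 12–14% |
| 0.8 | 38–43% |

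The ranges cover repeated runs with either test. Adding the protocol's OTP ICC of 15% leaves the results in these ranges (13% and 39% at 0.5 and 0.8 SD with the joint test). The median spurious share mediated is 3.5% at 0.5 SD and 9.8% at 0.8 SD.

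**5. Does lagging alone cure it?** Not fully, because counselors who adopted before the midpoint have raised scores and also go on delivering. With 2 later patients per counselor, reached at 42% for early adopters and 2% for others (assumed), g = 0.8 and no mediator effect, relating the midpoint score to later Reach still declares mediation in 6% of runs if a quarter of SSL counselors adopt before the midpoint, and in 24% if half do. In a separate illustrative run at 0.8 SD the rate fell from 42–59% (same wedge) to 4–14% (lag only). It reached about 0% only when earlier delivery was adjusted for or earlier adopters were excluded.

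**The case against.** The strongest reply is that which survey wave is set against which outcome period is ordinary analysis-plan content, and that plan is not shown. A reader might infer that the protocol pairs the end-of-Implementation survey with the same wedge's Reach and Adoption. No sentence says so. Correctly ordered data also exist: Maintenance is an Aim 1 outcome, and its 1200 pulls all follow the last survey. Both points stand, and they rule out saying that the design will produce false mediation.

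They do not dispose of the matter. Survey timing is fixed in the protocol, and no analysis plan can supply a wave taken after SSL exposure but before delivery. The mechanism is claimed for the main SSL effect, which for Reach and Adoption rests on the overlapping wedge. Maintenance, as Table 2 frames it, is a different contrast.

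A second reply is that the simulation is not this trial. The surveys are tied to each OTP's own crossover, so usual-care scores after a usual-care outcome period are not clearly available. The baseline wave and the latent-factor model are also left out, and the values of g are assumed. This stands. The percentages show what is possible under an assumed pairing; they are not error rates for this trial.

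Finally, Aim 3 is labelled exploratory, its mediators are called putative, and only partial explanation is hypothesized. This limits the weight of the point.

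**Conclusion.** The point holds in a limited form. From the protocol's own calendar, both post-baseline surveys follow the start of CM delivery, and the last follows all delivery counted in that wedge's Reach and Adoption. For those same-wedge outcomes, an association cannot separate mediator from consequence, and describing it as a mechanism of action claims more than the data can show.

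The size is unknown because it turns on how far delivering CM moves survey scores. In the illustration it is negligible below about 0.3 SD and material at 0.5 SD or more. The stronger conclusion, that Aim 3 will find false mediation in some stated share of trials, is not supported: the pairing and the effect sizes behind such a figure are assumptions. The primary and secondary aims are untouched. This is a worthwhile improvement to an exploratory aim, not a flaw in the trial.

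**What to change.** State in the Aim 3 analysis that a mediator must be measured before the outcome it is used to explain:

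- **Active phase.** Use the change from start of Preparation to mid-Implementation only against Reach and first CM delivery after the midpoint survey. Restrict this to counselors with no CM delivery before that survey, or adjust for that delivery.
- **Sustainment.** Use the end-of-Implementation survey only as a mediator of Maintenance, adjusted for active-phase CM delivery.
- **Same wedge.** Report associations between surveys and outcomes of the same wedge as correlational, not as mechanisms of action.

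The cost is wording; no survey is added, and the Trial status section reports that no organization or provider had been enrolled. The downsides are fewer active-phase events and, for Adoption, a selected set of later adopters. The analysis also needs session dates. The protocol names these only for the CM Tracking Tool, which OTPs may choose not to use; that the EMR encounter extract carries them is an assumption to confirm with the sites.

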#### Research team observational measures

Research staff will complete observational measures of implementation strategy progress (on an ongoing basis) and counselor fidelity to the CM model (at the end of the didactic workshop). These scales will enable us to examine the concordance between provider-self report and research staff observation.

### Study measures

To address Specific Aim 1 (implementation effectiveness), we measure the following implementation outcomes: Reach, Adoption, Implementation, Maintenance, and Equity [45]. To evaluate Specific Aim 2 (patient effectiveness), we measure two patient outcomes in line with the Effectiveness element of RE-AIM: Stimulant Abstinence and Treatment Retention. Finally, in pursuit of Specific Aim 3 (exploratory mediators), we evaluate contextual determinants as putative mediators of implementation outcomes; specifically, we assess implementation strategy progress, inner setting factors, and provider characteristics. Table 1 presents a detailed overview of study measures by Specific Aim.

**Table 1 Tab1:** Description of study measures, data source, and timing of measurement

Outcome	Definition	Data source	Frequency and timing of measurement
*Aim 1*			
Reach	Calculates patients’ exposure to contingency management (CM) by dividing the number of newly admitted patients with recent stimulant use (defined as documented patient-reported stimulant use or a positive stimulant urine screen within the first 30 days of treatment) who received 1 or more CM encounters by the total number of newly admitted patients with recent stimulant use.	Electronic medical records (EMR) CM tracking tool	End of each wedge
Adoption	Calculates the proportion of providers who have adopted CM by dividing the number of counselors who delivered 1 or more CM encounters divided by the total number of counselors.	EMR CM tracking tool	End of each wedge
Implementation	Assesses delivery of CM with fidelity in two ways: 1. Proportion of counselors meeting the fidelity target on the CM Competence Scale (a mean overall score ≥ 4.0), which rates 9 CM elements on a scale from 1 (not at all present) to 7 (fully present) 2. Proportion of CM sessions covering ≥ 7 of 9 of the standard CM elements, as assessed by a self-report checklist in the CM tracking tool.	Observer rating CM tracking tool	Role play following Preparation phase End of each wedge
Maintenance	Measures Reach, Adoption, and Implementation throughout the Sustainment phase.	EMR CM tracking tool Observer rating	End of each wedge during Sustainment phase
Equity	Evaluates whether the above systematically vary based on race/ethnicity, biological sex, gender, and other sociodemographic factors of patients and providers.	EMR Provider survey	Baseline
*Aim 2*			
Stimulant abstinence	Calculates abstinence rates as the number of urine screens that are negative for stimulants divided by the total number of urine screens received by patients with recent stimulant use.	EMR	End of each wedge
Treatment retention	Measures engagement with treatment in three ways for each patient: 1. Duration of time from patient intake to discharge in day 2. Proportion of scheduled encounters that the patient attended 3. Number of CM sessions received	EMR EMR CM tracking tool	End of each wedge
*Aim 3*			
*Implementation strategy progress*			
Stages of Implementation Completion (SIC) [46]	Evaluates completion of key activities for implementing the contingency management intervention across 8 stages. Two scores are calculated for each stage: proportion calculates the percent of activities completed within a stage and duration calculates time from date of entry through completion.	Process notes External facilitator report	Ongoing throughout Preparation and Implementation phase for each OTP
Cost of Implementing New Strategies (COINS) [47]	Calculates the fees, expenses, and person hours necessary to complete the implementation strategy as mapped onto SIC. Customized via a standardized adaptation approach.	Process notes External facilitator report	Ongoing throughout Preparation and Implementation phase for each OTP
*Inner Setting Factors*			
Implementation Climate Scale (ICS) [48]	Measures provider perceptions of the extent to which organizations expect, reward, and support implementation of CM. Scale includes 18 items scored on 5-point scales from 0 (not at all) to 4 (very great extent) divided into 6 subscales.	Provider surveys	Three timepoints for each OTP crossing into active support: Start of Preparation, Midpoint of Implementation, End of Implementation
Implementation Leadership Scale (ILS) [49]	Measures providers’ report of the extent to which leaders at their organization are aligned and visibly in support of CM. Scale includes 12 items, rated from 0 (not at all) to 4 (very great extent) divided into four subscales.	Provider surveys	Three timepoints for each OTP crossing into active support: Start of Preparation, Midpoint of Implementation, End of Implementation
Inventory of Factors Affecting Successful Implementation and Sustainment (IFASIS)	Assesses barriers and facilitators to implementation via a team-based inventory collaboratively completed by each OTP at a leadership team. Consists of 27 items each scored in two ways: rating, scored on a 5-point scale ranging from 1 (least positive) to 5 (most positive), and importance, scored on a 3-point scale ranging from 1 (not important) to 3 (very important).	Recorded by leadership team	Three timepoints for each OTP crossing into active support: Start of Preparation, Midpoint of Implementation, End of Implementation
*Provider characteristics*			
AIM, IAM, FIM [50]	Measures the extent to which providers view CM as acceptable (Acceptability of Intervention Measure [AIM]), appropriate (Intervention Appropriateness Measure [IAM]), and feasible (Feasibility of Intervention Measure [FIM]). Each measure contains 4 items scored on a 5-point scale ranging from 1 (completely disagree) to 5 (completely agree).	Provider surveys	Three timepoints for each OTP crossing into active support: Start of Preparation, Midpoint of Implementation, End of Implementation
CM Attitudes Scale	Measures provider attitudes and objections towards CM via a 5-item survey; three items range from 1 (strongly disagree) to 7 (strongly agree), one item ranges from 1 (complete unacceptable) to 7 (very acceptable), and the final item ranges from 1 (not at all effective) to 7 (very effective).	Provider surveys	Three timepoints for each OTP crossing into active support: Start of Preparation, Midpoint of Implementation, End of Implementation
Provider demographics	Assesses a range of sociodemographic variables, including sex/gender, race/ethnicity, age, tenure at the OTP, licensure status, and years in the addiction health services field.	Provider survey	Baseline

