The SSL has demonstrated effectiveness in promoting the implementation of CM targeting attendance [20], but has never been evaluated for the implementation of CM targeting stimulant use. Furthermore, prior SSL studies have been subject to several limitations. First, previous investigations have confounded receipt of the SSL implementation strategy with provision of CM resources by providing OTPs a fully stocked prize cabinet at the start of implementation [20, 21, 24]. Second, SSL trials have only measured sustainment for up to 6 months [24], which limits conclusions about the ability of OTPs to continue CM implementation without active support. Finally, studies of the SSL have not rigorously tracked adherence to implementation strategy [20, 21, 24]. The current project will address these three gaps by: decoupling the SSL strategy from the provision of incentives; using a stepped wedge design that enables monitoring of sustainment over a longer time horizon; and rigorously specifying and tracking the SSL strategy.

Our protocol is guided by three specific aims:Specific aim 1 (primary aim): to test the effectiveness of the SSL on implementation outcomes. It is hypothesized that receipt of the SSL will be associated with significant increases in: CM Reach (percent of patients receiving CM), CM Adoption (percent of providers delivering CM), and CM Maintenance (reach and adoption after removal of active support).Specific aim 2 (secondary aim): to test the effectiveness of the SSL on patient outcomes. It is hypothesized that receipt of the SSL will be associated with significant increases in: Stimulant Abstinence (percent of stimulant-negative screens) and Treatment Retention (number of treatment sessions).Specific aim 3 (exploratory aim): to evaluate contextual determinants, including SSL adherence, as putative mediators of implementation outcomes. It is hypothesized that contextual factors at the organization-level (e.g., implementation climate, leadership) and provider-level (e.g., perceptions of CM) will partially explain the effect of the SSL on implementation (Aim 1) outcomes.

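### Session fidelity (Implementation measure 2) is labelled a proportion of CM sessions but is observable only for sessions logged in an opt-in tool, so its level and its change into Sustainment cannot be read without coverage

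*Protocol article*

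**What the plan says.** **Definition and source.** In Study measures, Table 1, Implementation has two measures. The first is an observer rating of counselors in a role play after Preparation. The second is session-based: "Proportion of CM sessions covering ≥ 7 of 9 of the standard CM elements", "as assessed by a self-report checklist in the CM tracking tool". The Implementation row names observer rating and the tracking tool as sources. Unlike the Reach and Adoption rows, it does not name the EMR.

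**Status of the tool.** EMR extraction and CM tracking tool says that "those OTPs that opt to use the tool will be asked to send the Excel tracker at the same six time points". The same section has every OTP record CM sessions in its own EMR and extract all patient encounters at six time points. Under Implementation phase, Performance feedback, "The CM Tracking Tool is used as the basis of a recommended EMR build for the OTPs", so the build is advised and not required. In Sustainment phase, OTPs keep access to the tool, but nothing obliges them to use it.

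**Use in Maintenance.** Table 1 carries the measure forward, since Maintenance "Measures Reach, Adoption, and Implementation throughout the Sustainment phase". The Aim 1 hypothesis in Background is narrower: "CM Maintenance (reach and adoption after removal of active support".

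**Content of the checklist.** On the tool, Performance feedback states: "It also contains the first 6 items of the CM Competence Scale".

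**The concern.** The label promises a proportion of all CM sessions, while the named source yields a proportion of logged ones. OTPs that do not take up the tool, and sessions a counselor does not log, are absent from both numerator and denominator. In Sustainment a second selection is added: an OTP that has stopped CM has no sessions and drops out of the figure.

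Measure 2 is the only fidelity measure taken on actual sessions, and the main one repeated after active support ends. A move in it between phases could reflect a change in how CM is delivered, in who logs, or in which OTPs still offer CM. As Table 1 stands, the reported proportion would not separate these.

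**Working it through.** The protocol states no expected fidelity, opt-in share or logging share. In Data analysis, Table 2, Implementation has no planned comparison and the Maintenance row has no predicted rate or power. There is therefore no planned figure to reproduce. The values below are assumptions, except the 22% Reach, which is Table 2's predicted rate for Preparation/Implementation.

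**1. Bounds from incomplete logging.** Let *s* be the share of CM sessions with a checklist and *p* the proportion adequate among them.
- Lower bound (all unlogged sessions inadequate) = *s* × *p*
- Upper bound (all unlogged sessions adequate) = *s* × *p* + (1 − *s*)

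The width is 1 − *s*, whatever the value of *p*. With *p* = 80%:

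| Share logged | Lower | Upper |
|---|---|---|
| 80% | 0.8 × 0.8 = 64% | 64% + 20% = 84% |
| 50% | 0.5 × 0.8 = 40% | 40% + 50% = 90% |
| 30% | 0.3 × 0.8 = 24% | 24% + 70% = 94% |

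**2. Change between phases.** Suppose logged fidelity is 80% in both phases, with 80% of sessions logged in the Implementation phase and 50% in Sustainment. The reported change is zero. The true change could lie between 40 − 84 = −44 points and 90 − 64 = +26 points.

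**3. OTPs that stop CM.** Take ten OTPs of equal volume with full logging, 22% Reach everywhere in the active phase, and average fidelity 70%. Five stop CM in Sustainment, so Reach falls to 22% × 5/10 = 11%.

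| Fidelity of stopping / continuing OTPs | Measure 2, active phase | Measure 2, Sustainment |
|---|---|---|
| 50% / 90% | (5 × 50 + 5 × 90)/10 = 70% | 90% |
| 70% / 70% | 70% | 70% |
| 80% / 60% | (5 × 80 + 5 × 60)/10 = 70% | 60% |

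No OTP changes its practice in any row, yet the measure rises, stays level or falls according to which OTPs remain. Reach halves in all three.

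**4. The threshold.** The tool holds six Competence Scale items, while the threshold is at least seven of nine elements. Read literally, no session logged in the tool could meet it.

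**The case against.** **A reader might infer that Maintenance could look good while CM is collapsing.** The documents do not support that. Maintenance in Table 1 is three separate measures with no composite. Reach divides "by the total number of newly admitted patients with recent stimulant use" and Adoption divides by all counselors. Neither denominator shrinks when CM stops, and both list the EMR as a source. In the scenario above, Reach at 11% stands under the same heading as the fidelity figure.

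**A reader might also infer that the Aim 1 tests are biased.** They are not. The Maintenance hypothesis rests on reach and adoption, and no comparison is planned for Implementation.

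**Nor is upward bias established.** It needs the sessions or OTPs that drop out to be worse than those that remain. That is plausible, but the documents give nothing to show it.

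**Conditioning on delivered sessions is normal for fidelity.** How well CM is delivered is a different question from how many patients receive it, and the protocol rightly keeps the two apart. This stands, and it argues against replacing the session measure with one per eligible patient.

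**The EMR may hold the items.** The EMR section lists implementation among the variables to be calculated from patient records, the Maintenance row names the EMR as a source, and an OTP that adopts the recommended build might record the checklist there. This softens the point but does not remove it: the build is not required, and Table 1 ties measure 2 to the tool.

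**Coverage reporting is often left to the analysis plan.** True, but the article itself fixes the measure and its source, and there the label and the source disagree.

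**Conclusion.** The point holds for measure 2 alone. It is labelled a proportion of CM sessions, but by its stated source it describes logged sessions at OTPs that use the tool. Its level is uncertain by the unlogged share: 40% to 90% if half of sessions are logged and 24% to 94% if 30% are, when logged sessions show 80% adequate. Its change into Sustainment can go either way through selection alone. These sizes rest on assumed logging shares and site fidelities.

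Reach, Adoption and the hypotheses built on them are untouched. The matter is one of interpreting a descriptive Aim 1 measure, and the remedy is a cheap improvement. The mismatch between six items and a 7-of-9 threshold is a separate and more basic conflict that must also be settled.

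**What to change.** - In Table 1, count CM sessions for measure 2 from the EMR extract at all ten OTPs.
- By OTP and phase, report the logged-only proportion, the share of EMR-recorded CM sessions with a checklist, and the lower and upper bounds (all unlogged inadequate; all unlogged adequate). Give the number of contributing OTPs for each phase.
- State that a change in measure 2 during Sustainment will not be interpreted without Reach and Adoption beside it. The EMR count alone does not cover this, because an OTP that has stopped CM has no sessions in the EMR either.
- Keep session fidelity as the Maintenance component. Adequate-fidelity CM per eligible patient may be added as a supplementary descriptive figure. It should not be substituted, because it folds Reach into fidelity and needs a patient-level rule for adequacy that the protocol does not contain.
- Reconcile the tool's six items with the 7-of-9 threshold before measure 2 is scored.

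**Cost.** For the denominator, coverage and bounds, wording in Table 1 and the analysis plan. The EMR encounters are already to be extracted, and aggregate session counts suffice, so tracker records need not be linked to EMR records. This relies on OTPs recording CM sessions in the EMR as the protocol asks. The downside is a less favourable figure, with wide bounds where the tool is little used.
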